#### Randomization and blinding

Patients will be randomized at a ratio of 1:1:1 among the three intervention arms: follow-up by telephone, follow-up using a smartphone game, or follow-up with usual care in the public health system. Random allocation will be performed in blocks with variable sizes, stratified by participants with and without smartphone access. Randomization will be performed using R software [18]. Individuals who have access to a smartphone will be randomly assigned to any of the 3 groups, while individuals without access to a smartphone will be randomly assigned to one of only two groups: the telephone follow-up group or the control group.

An independent statistician will be responsible for computerized randomization (R software [18]) but will not be involved in the determination of participant eligibility, assessment or implementation of the interventions. Blinding will be applied to minimize bias. Allocation concealment as the person responsible for the randomization will be applied to the randomized group only after the participants have been recruited, which will occur after baseline measurements are completed. Researchers responsible for the follow-up by telephone intervention will not have access to performance and evaluation data. Only the biostatistician will have access to the data stored in the data entry system, minimizing investigator influence.

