## Materials and methods

### Study design

The SIM study is a single-center, superior, randomized controlled trial with a 1:1:1 allocation ratio that includes three parallel arms: (1) follow-up with telephone calls, (2) follow-up using gamification in a mobile app, and (3) follow-up with usual care provided by the public health system. The conventional strategy in Brazil involves through mandatory notification by the physician and guidance to the patient, but it does not consist of an active search through home visits or telephone contacts. Randomization will occur at the individual level.

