### Sample size

Considering a confidence level of 95%, an incidence rate of 93.7 per 100,000 inhabitants in the municipality of Porto Alegre [9], and an acceptable difference of 60.0 per 100,000 inhabitants, it is estimated that testing 10,000 individuals will be necessary to obtain an accurate prevalence of syphilis in the municipality. This sample will serve as the basis for the inclusion of patients in the clinical trial.

For the randomized clinical trial, another sample size calculation will be considered. Using a previous article in which 16.5% of the participants who were diagnosed with syphilis received appropriate treatment and 55.9% received inappropriate treatment as a reference, it is expected that at least half of the latter group will eventually receive proper treatment, for a total of 44.45% receiving appropriate treatment [17]. Thus, considering a sample size calculation to detect differences in the proportions of adequate treatments between groups, using a 95% confidence level, 80% power, and a maximum loss rate of 20%, 51 participants in each study group will be needed.

The primary goal of the study is to compare treatment adherence and follow-up among the three parallel study arms. The groups will be compared as a whole, and if relevant, pairwise analysis will be conducted. Such comparisons will be performed using the chi-square test and adjusted residuals when necessary. We will investigate the association between treatment

adherence and sociodemographic, sexual health, and sexual behavior variables as secondary outcomes. The association will be estimated by calculating crude and adjusted odds ratios (ORs) using logistic regression, also addressing confounding variables. Intention-to-treat analysis will be used to assess the clinical effectiveness of the intervention.

We anticipate a minimal number of missing values given that the study variables will be collected by trained researchers. However, data quality analysis will be applied to identify inconsistencies and missing data, and meetings with the researchers will be conducted to discuss missing data and prevent further inconsistencies.

A statistical significance level of 0.05 will be adopted for all statistical analyses. R software, version 4.0.3, will be used for the analysis.

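### The app arm can hold only smartphone owners, but the planned chi-square tests ignore smartphone access, so both app contrasts and the three-arm test are confounded if access predicts adherence

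*Protocol article*

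**What the plan says.** Under Study design, the protocol article describes a "randomized controlled trial with a 1:1:1 allocation ratio", and Randomization and blinding repeats the 1:1:1 ratio. The latter section then stratifies by smartphone access. Owners may go to any of the three arms, but "individuals without access to a smartphone will be randomly assigned to one of only two groups: the telephone follow-up group or the control group".

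The Introduction plans three contrasts: app versus telephone, app versus conventional care, and telephone versus conventional care. The main hypothesis is that the game does best. Under Sample size, the arms are to be compared as a whole and then, if relevant, in pairs: "Such comparisons will be performed using the chi-square test and adjusted residuals when necessary". Statistical analyses again names chi-square and Fisher's exact tests for proportions. Neither section limits the app contrasts to owners or stratifies the test. Crude and adjusted odds ratios appear in both sections, but for associations of adherence with sociodemographic, sexual health and behaviour variables, as secondary outcomes. Smartphone access is not named among them.

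The sample size statement ends: "51 participants in each study group will be needed". No trial total is given.

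**The concern.** The chance of entering the app arm depends on the stratum: one third for owners under equal allocation, zero for non-owners. Pooling the strata without adjustment makes each app contrast a mixture of a randomised comparison and a built-in difference in smartphone access. If access goes with income, age or education, and through them with finishing treatment, the app arm will look better or worse with no effect of the app. More recruitment does not remove this bias. Intention-to-treat does not either, because the imbalance arises at assignment.

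At stake are two of the three pairwise contrasts, including both that test the game, and the global test that precedes them. In addition, an unqualified 1:1:1 does not describe a design in which one stratum is randomised 1:1.

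**Working it through.** **1. The plan's own figure.** Inputs from Sample size: "16.5% of the participants who were diagnosed with syphilis received appropriate treatment and 55.9% received inappropriate treatment as a reference", and the target "for a total of 44.45% receiving appropriate treatment", which is 16.5 + 55.9/2 = 44.45%. The difference is 27.95 points, at significance level 0.05 (taken as two-sided) and 80% power. With p̄ = 0.30475:

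n = [1.96·√(2p̄(1−p̄)) + 0.8416·√(p₁q₁ + p₂q₂)]² / Δ² = [1.96·0.6510 + 0.8416·0.6202]² / 0.2795² = 41.4, so 42 per arm.

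42 × 1.2 = 50.4, so 51. The figure of 51 reproduces.

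**2. Arm sizes.** Let u be the share without a smartphone. The documents do not give it, so 5% to 30% is assumed. Also assumed are N = 3 × 51 = 153 and equal allocation within each stratum.

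- App = N(1−u)/3.
- Telephone = control = N(1−u)/3 + Nu/2.
- Non-owner share of telephone and of control: f = (u/2) / [(1−u)/3 + u/2].

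At u = 20%: app 40.8; the other arms 40.8 + 15.3 = 56.1 each; f = 15.3/56.1 = 27.3%.

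**3. Bias with no app effect.** Bias = f × (completion in owners − completion in non-owners). The completion rates are assumptions. At u = 20% with 35% versus 15%: 0.273 × 20 = 5.5 points.

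**4. Type I error of the crude app-control test.** Normal approximation after 20% loss. At u = 20%, n is 32.6 and 44.9, the expected rates are 35% and 29.5%, the null standard error is 0.107 and the actual one 0.108. The critical difference is 1.96 × 0.107 = 0.210. The rejection probability is P(Z > (0.210 − 0.055)/0.108) + P(Z < (−0.210 − 0.055)/0.108), about 0.074 + 0.007 = 8.1%.

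| u | App / each other arm | f | Completion, owners vs non-owners | Bias (points) | Type I error |
|---|---|---|---|---|---|
| 5% | 48 / 52 | 7% | 35% vs 15% | 1.5 | about 5.2% |
| 10% | 46 / 54 | 14% | 35% vs 15% | 2.9 | 5.4–5.9% |
| 20% | 41 / 56 | 27% | 35% vs 15% | 5.5 | about 8% |
| 30% | 36 / 59 | 39% | 35% vs 15% | 7.8 | about 11.5% |
| 30% | 36 / 59 | 39% | 45% vs 15% | 11.7 | about 18% |

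The range at 10% spans the exact binomial calculation and the normal approximation.

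**5. Telephone versus control.** Both arms have the same expected f, so the bias is f × gap − f × gap = 0. Ignoring the stratum here affects efficiency, not validity.

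**6. The owners-only app-control contrast.** If the total were fixed at 153, each arm would have n = 0.8 × 153(1−u)/3 evaluable owners: 36.7, 32.6 and 28.6 at u = 10%, 20% and 30%. Power = Φ{[0.2795·√n − 1.96·0.6510] / 0.6202} = 75%, 70% and 64%. With u = 0 (n = 40.8) the same formula gives 79%. To randomise 51 owners to each arm, total enrolment would be 153/(1−u): about 170, 191 and 219.

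**The case against.** **Sample size.** A reader might infer that 51 per arm is unreachable and that 80% power is lost. The documents do not support that. They set a requirement per group and state no total. Recruiting until the app arm reaches 51 meets the text, and a sample size recalculation is foreseen at the six-month interim analysis. The figure of 153 is only 3 × 51. The 75%, 70% and 64% apply only if that total is fixed, and only to the owners-only contrast. The crude contrast at 153 would keep about 78%, 77% and 75% if smartphone access were unrelated to adherence. This objection stands.

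**Ratio.** The ratio among owners is not stated separately. An overall 51:51:51 is possible if owners are over-allocated to the app. At 20% without smartphones, 51 of about 122 owners would go to the app and about 36 to each other arm. Owners would then be 70% of those arms, and a 20-point gap would give a bias of 6 points rather than 5.5. So 1:1:1 is unqualified rather than impossible, and forcing it slightly worsens the confounding.

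**Size of the bias.** No document gives the smartphone share or ties it to adherence. Excluding illiterate people and those without contact information may lower the non-owner share. The harm could be small. This also stands.

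**Adjustment.** Logistic regression that addresses confounding is planned, and an analysis plan not shown here may add detail. But the adjusted model belongs to the secondary associations, and the protocol does not leave the primary test open: it names an unstratified one. This does not answer the point.

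**Conclusion.** The structural point holds. The stated primary test disregards a factor on which the allocation probability depends, so app versus telephone, app versus control and the global test are not purely randomised comparisons. Telephone versus control is.

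The size is conditional. It needs smartphone access to predict adherence, and it grows with a share that the documents do not give. Under the assumptions above, it runs from negligible at 5% without smartphones to a bias of 7.8 points at 30%, or 11.7 points with the wider completion gap. The design difference is 27.95 points. The direction of bias depends on which group adheres better. Bias and type I error were computed for app versus control only. The bias is the same for app versus telephone under the same no-effect assumption, and no figure was derived for the global test.

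The 51 per group is not wrong. What is unclear is whom it counts. The change is needed because, as written, the comparisons that test the main hypothesis rest on smartphone access being irrelevant to adherence.

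**What to change.** - Run app versus telephone, app versus control and the three-arm global test among smartphone owners only.
- Run telephone versus control in all participants, stratified by smartphone access (Cochran-Mantel-Haenszel test, or logistic regression with the stratum as a term).
- Replace the unqualified 1:1:1 with the ratio within each stratum: 1:1:1 with a smartphone, 1:1 without.
- State that the 51 per group refers to smartphone owners. If the total is instead fixed at 153, restate the power of the app contrasts (about 75%, 70% or 64% at 10%, 20% or 30% without smartphones).

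The cost is mostly wording. Smartphone access must already be known at randomisation, so no new data are needed. The drawback is that non-owners no longer contribute to the app contrasts, whose power falls unless the 51 per group is counted in owners. Counting it that way raises total enrolment to about 170, 191 or 219 at the same three shares.

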#### Intervention

The intervention strategies aim to increase adherence to treatment and monitoring and promote communication with sexual partners (Fig. 1). All intervention and conventional strategies followed the guidelines of the Clinical Protocol and Therapeutic Guidelines for Comprehensive Attention to People with Sexually Transmitted Infections of the Ministry of Health of Brazil [4].

**Fig. 1 Fig1:**
[figure not shown]
Profile of study

#### Strategy 1: Follow-up by telephone

Initial contact will be made 2 days before treatment, on the day of treatment and for 14 days until the next treatment dose. If the patient fails to apply treatment within 14 days of the last treatment dose, the intervention will be considered a failure, and the patient will have to restart treatment. For monitoring, contact will be made 7 days before the exam and on the day of the exam to encourage the patient to get tested, and the patient will receive 1 call per week for 3 weeks until the patient takes the VDRL test.

#### Strategy 2: Follow-up using a game in a smartphone app

A thematic game will be developed to encourage treatment and monitoring in patients with syphilis. The game will be easy, similar to other commercial games such as Candy Crush (King), Bubble Shoote (Sukavaty), Block Puzzle (Honkong Sanyou), and Block Puzzle Jewel-puzzle game (Elimination Master) and can be played by different ages and different education levels. The first phase of the game will be open to all study participants regardless of their rapid test results and will have information about prevention strategies and sexually transmitted infections. In the second phase, the participants will be prompted by notifications via smartphone 2 days before the day of treatment, on the day of treatment, and every day for 14 days after the date they should have received the injection. The participant is awarded coins to buy clothing and accessories for his or her avatar if he or she reads the information about STIs and provides information about his or her partners. The participant passes the phase of the game when he or she has taken the medication doses and completed the VDRL test. In different game phases, the avatar takes the bus and travels to different capitals of Brazil, where syphilis infection rates are also high.

#### Strategy 3: Conventional follow-up

The conventional strategy involves compulsory notification by a healthcare professional, and the patient is directed to seek treatment and follow-up at the primary health care unit closest to his or her home. The outcomes will be accessed by reviewing data from the public health records.

### Outcome assessment

Compliance with treatment for those in the mobile app arm will be assessed according to the uploaded game data provided by the participant and use of the app during the study period. Adherence to treatment for those receiving telephone follow-up will be assessed through routine phone calls and questionnaire questions about the date of examination and treatment. Adherence in the usual care arm will be assessed by information collected from the participant's medical record at their referral health unit. The primary outcome will be the percentage of the participants who finish all three doses of penicillin in the 3 weeks. The secondary outcome will be the percentage of participants who completed VDRL tests at 3, 6, and 12 months. We also evaluated the number of sexual contacts informed by each participant. The outcomes will be evaluated by self-declaration and by contacting the healthcare unit where the participants made treatment and follow-up.

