### Study procedures

A paper-based questionnaire to collect sociodemographic, behavioral, and health information will be administered to all participants to check eligibility, and a rapid test for syphilis will be performed. All participants with a positive test result will undergo confirmatory testing. Upon the receipt of confirmatory test results, the participants will be invited to take part in the clinical trial, and a web-based questionnaire will be used to collect information such as age, sex, social class, education level, alcohol consumption, tobacco and drug use, risk for syphilis, history of hepatitis and other sexually transmitted infections (STIs), number of sexual partners, type of sex and condom use. The main objective of the trial is to test strategies to improve adherence to follow-up. Overall, to increase awareness regarding syphilis, all participants will receive informative folders on syphilis, HIV, and hepatitis prior to randomization. Adherence will be monitored by the number of accesses to the application and by successful telephone calls.

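### Treatment adherence is assessed from a different source in each arm, and the article does not say which source decides the primary outcome

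*Protocol article*

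**What the plan says.** The Outcome assessment section of the protocol article defines the primary outcome: "The primary outcome will be the percentage of the participants who finish all three doses of penicillin in the 3 weeks". The secondary outcome is completion of VDRL tests at 3, 6 and 12 months.

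The same section gives one assessment rule per arm:

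- App: "Compliance with treatment for those in the mobile app arm will be assessed according to the uploaded game data provided by the participant", with use of the app as a further component.
- Telephone: "Adherence to treatment for those receiving telephone follow-up will be assessed through routine phone calls and questionnaire questions". The questions concern the dates of examination and treatment.
- Usual care: the participant's medical record at the referral health unit. Strategy 3: Conventional follow-up agrees: "The outcomes will be accessed by reviewing data from the public health records".

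The section closes with a general sentence: "The outcomes will be evaluated by self-declaration and by contacting the healthcare unit where the participants made treatment and follow-up". It names no arm, gives no order of precedence and does not withdraw the arm-specific rules.

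The Sample size and Statistical analyses sections then compare the arms directly on these proportions. The comparison is an overall chi-square test, with pairwise comparisons where relevant.

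**The concern.** Source and arm coincide completely. In both intervention arms, the channel that delivers the intervention also supplies the adherence data. Neither randomization nor intention-to-treat analysis nor a chi-square test can separate more doses received from more doses reported.

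All three contrasts named in the Introduction are exposed: app against usual care, telephone against usual care, and app against telephone. VDRL completion is affected too, because the telephone questions cover examination dates and the Strategy 3 sentence applies to outcomes in general.

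If data from a common source are not collected, no later analysis can repair this. At stake is whether a positive result would show better treatment completion or only a more generous way of recording it.

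**Working it through.** **The plan's own figure.** The inputs from the Sample size section are 16.5% against 44.45% (16.5 + 55.9/2), 80% power, 95% confidence and 20% loss. The two-sided pooled-variance formula gives 41.4, so 42 per arm. Multiplying by 1.2 gives 50.4, rounded up to the stated 51; dividing by 0.8 gives 53. The sample size is not at issue. The planned difference is 44.45 − 16.5 = 27.95 points. After 20% loss, 51 × 0.8 = 40.8, so about 41 per arm remain.

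**Error model.** All error rates are assumed, because the article gives none. Let t be true completion, equal in every arm. Let f be the share of non-completers recorded as complete in an intervention arm, and s the share of true completers captured there. Let r be the share of true completers captured by the records.

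- Observed intervention proportion = t·s + (1 − t)·f
- Observed usual-care proportion = t·r

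The rejection probability is the exact binomial probability that a two-sided 5% chi-square test of intervention against usual care is significant. The article does not state sidedness, so two-sided is assumed.

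| Assumed scenario | Intervention | Usual care | Spurious difference | Rejection, 41 / 51 per arm |
|---|---|---|---|---|
| t=0.30, s=1, f=0.20, r=0.90 | 0.30 + 0.70×0.20 = 0.44 | 0.30×0.90 = 0.27 | +17 points | 0.368 / 0.441 |
| t=0.30, s=1, f=0.10, r=1 | 0.30 + 0.70×0.10 = 0.37 | 0.30 | +7 points | 0.103 / 0.117 |
| t=0.30, s=0.70, f=0, r=1 | 0.30×0.70 = 0.21 | 0.30 | −9 points | 0.155 / 0.183 |
| t=0.30, s=0.70, f=0.10, r=0.90 | 0.21 + 0.07 = 0.28 | 0.27 | +1 point | 0.051 / 0.053 |

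**At the article's own completion rates**, with s=1, f=0.10 and r=0.90:

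- t=0.165: 0.2485 against 0.1485, a spurious 10.0 points, rejection 0.243 at 51 per arm.
- t=0.4445: 0.500 against 0.400, a spurious 10.0 points, rejection 0.191 at 51 per arm.

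**One source with equal error in every arm.** The spurious difference is 0 and rejection stays at about 0.05.

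**Effect of the overall test.** The figures above are for a single pairwise test. Suppose both intervention arms are inflated equally and the pairwise test counts only after a significant three-arm chi-square. By simulation, the first scenario then falls to about 28% / 35% and the second to about 6% / 7% (41 / 51 per arm).

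**The case against.** The strongest reply is that the closing sentence of Outcome assessment already supplies a common source. On that reading, the three arm-specific sentences describe tracking during follow-up, and health-unit contact settles the outcomes in every arm. The reading is possible, and if the text said so the problem would largely disappear. It does not: the sentence puts self-declaration beside the health unit without ranking them, and the arm-specific rules remain in force.

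A second reply concerns direction, and it stands. A reader might infer that the bias must favour the interventions. A participant who received every dose but stopped uploading, or did not answer calls, could be counted as a non-completer. The third scenario above then makes the app arm look worse, and the fourth nearly cancels the errors.

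Other stronger readings are tempting, but the text does not establish them:

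- Study procedures says: "Adherence will be monitored by the number of accesses to the application and by successful telephone calls". This can be read as adherence to the intervention, and it does not redefine the three-dose outcome.
- Randomization and blinding says: "Researchers responsible for the follow-up by telephone intervention will not have access to performance and evaluation data". A contradiction with assessment by telephone might be inferred. However, callers can log answers without seeing the evaluation data, and the article does not say who administers the questionnaire.
- Strategy 2 lets a participant pass a phase once doses and VDRL are done. That false dose entries are rewarded does not follow, because the article does not describe how completion is verified. Coins are tied to reading the information and to partner details.
- Those coins might seem to bias the sexual-contacts outcome, but nothing says that outcome is counted from game entries.

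Finally, the size depends wholly on assumed error rates, and testing overall first lowers it.

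**Conclusion.** The point stands in this form: the article sets a different adherence source for each arm, adds a general sentence that does not resolve the difference, and so leaves the primary comparison mixed with the method of measurement. This should be corrected before outcome data are gathered, because it touches every contrast on the primary outcome.

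Over-report in the intervention arms and gaps in the usual-care records are the likelier errors, and both favour the hypothesis. That direction is plausible, not certain, least of all for the app arm.

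The size cannot be known from the article. With equal true completion of 30%, the assumed scenarios run from a spurious 17 points in favour of an intervention (37% to 44% false positives per pairwise contrast, before any gating on the overall test) to 9 points against it. The milder case of 10% over-report with perfect records gives 7 points and 10% to 12%. Against a planned difference of 27.95 points, errors at the upper end are material.

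**What to change.** State in Outcome assessment that dose dates and VDRL test dates in the health-unit record decide the primary outcome and VDRL completion in all three arms. The records should be sought in the same way in every arm and abstracted on one form that does not show the arm. Keep game uploads, app accesses and telephone self-report as process measures or for a sensitivity analysis. Reword Strategy 3 and the arm-specific and closing sentences of Outcome assessment so that they agree.

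The cost is a wording change plus record abstraction in the two intervention arms, which the planned health-unit contact already suggests. The sample size calculation is not altered by naming one source. The downside is that doses missing from records are missed, which may dilute a true difference. That loss is non-differential only if the treating unit is identified equally well in every arm. Active contact may identify it better than usual care does, so the procedure for finding the unit should also be the same in every arm.

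### The protocol names a different source of treatment adherence for each arm and no deciding source for the primary outcome, so measurement error can differ by randomized arm and bias every contrast

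*Protocol article*

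**What the plan says.** The Outcome assessment section of the protocol article gives treatment adherence three sources, one per arm.

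- App: "Compliance with treatment for those in the mobile app arm will be assessed according to the uploaded game data provided by the participant", to which the same sentence adds use of the app.
- Telephone: "Adherence to treatment for those receiving telephone follow-up will be assessed through routine phone calls and questionnaire questions". The questions cover the dates of both examination and treatment.
- Usual care: "Adherence in the usual care arm will be assessed by information collected from" the participant's "medical record at their referral health unit". The section on Strategy 3 words it more broadly: "The outcomes will be accessed by reviewing data from the public health records".

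The same section then defines the primary outcome (the percentage who finish all three penicillin doses in 3 weeks) and the secondary outcome (VDRL completion at 3, 6 and 12 months). It closes with a sentence that names no arm: "The outcomes will be evaluated by self-declaration and by contacting the healthcare unit where the participants made treatment and follow-up". It does not say whether both sources are used for everyone, which of them decides, or what happens when they disagree.

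**The concern.** The source of information changes with the randomized arm. A comparison of either intervention with usual care is then also a comparison of self-report with a record. The app and telephone arms differ in source too, so the contrast between them, which is part of the main hypothesis in the Introduction, is also exposed.

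The sources are likely to fail in different ways. Self-report can credit doses that were not given. A record can miss doses that were given elsewhere or not entered. Uploads and calls can miss a participant who was treated but stopped using the app or did not answer. If these errors are unequal, the arms can differ on the primary outcome when treatment does not. This is bias and not noise: intention-to-treat analysis keeps participants in their arms but does not correct how they were measured, and a larger sample only makes the biased difference easier to declare significant. The abstract's conclusion foresees a possible change in Brazilian health policy if differences are found.

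**Working it through.** **Inputs from the protocol (Sample size section).** Appropriate treatment 16.5% at reference and 44.45% expected (16.5 + 55.9/2); 95% confidence; 80% power; 20% loss; 51 per group; chi-square test at 0.05.

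**The plan's own figure.** With a two-sided test and no continuity correction, the mean proportion is (0.165 + 0.4445)/2 = 0.30475 and the difference is 0.2795.

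n = [1.96·√(2·0.30475·0.69525) + 0.8416·√(0.165·0.835 + 0.4445·0.5555)]² / 0.2795² = 41.4, so 42 per group. Then 42 × 1.2 = 50.4, so 51. The stated size is reproduced and this point does not alter it.

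**Assumed inputs.** The protocol gives no error rate for any source, so these are a range and not estimates:

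- F: share of non-completers counted as completers in an intervention arm.
- C: share of true completers captured in an intervention arm.
- R: share of true completers found in the usual-care record.

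**Model.** True completion p is the same in every arm.

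- Observed intervention rate = p·C + (1 − p)·F
- Observed usual-care rate = p·R

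Example with p = 0.165, F = 10%, R = 90%, C = 80%: 0.132 + 0.0835 = 0.2155 against 0.1485, a spurious gap of 6.7 points.

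The last column is the exact binomial probability, at 51 per arm, that the uncorrected two-sample chi-square is significant at two-sided 0.05 in favour of the intervention. It is 2.4% when nothing is misclassified.

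| F | R | C | Intervention | Usual care | Gap (points) | Falsely favours intervention |
|---|---|---|---|---|---|---|
| 5% | 100% | 100% | 20.7% | 16.5% | +4.2 | 7.6% |
| 10% | 100% | 100% | 24.9% | 16.5% | +8.4 | 17.8% |
| 10% | 90% | 100% | 24.9% | 14.9% | +10.0 | 24.2% |
| 20% | 100% | 100% | 33.2% | 16.5% | +16.7 | 50.7% |
| 20% | 80% | 100% | 33.2% | 13.2% | +20.0 | 68.5% |
| 10% | 90% | 80% | 21.6% | 14.9% | +6.7 | 13.6% |
| 5% | 90% | 70% | 15.7% | 14.9% | +0.9 | 3.2% |
| 0% | 90% | 70% | 11.6% | 14.9% | −3.3 | 0.7% |

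**Sensitivity to the true rate.** At p = 44.45% the first five rows give 5.4%, 9.2%, 19.0%, 22.3% and 55.9%. Under-capture weighs more there because there are more completers to miss. For the sixth row, 0.4445·0.8 + 0.5555·0.1 = 0.411 against 0.4445·0.9 = 0.400, a gap of only 1.1 points. For the last row, 0.311 against 0.400 gives −8.9 points.

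**Three-arm test.** If both intervention arms carry the third row's errors (p = 16.5%), the overall chi-square rejects in 22.4% of simulated trials at 51 per arm and in 18.0% at 41 per arm (after 20% loss).

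**One common source.** With the same method in every arm and no differential error, false rejection at 51 per arm returns to 4.8–5.8% pairwise and 4.8–4.9% for the three-arm test.

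**VDRL.** The telephone sentence covers examination dates, and Strategy 3 covers all usual-care outcomes. The app sentence covers treatment only. A VDRL source for that arm can only be inferred from the Strategy 2 rule that a game phase is passed once doses and VDRL are complete.

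**The case against.** The strongest reply is that a common source is stated. The closing sentence follows the outcome definitions and excepts no arm. Study procedures treats app accesses and successful calls as monitoring. Randomization and blinding keeps the telephone staff away from evaluation data. On that reading the arm-specific sentences describe monitoring, and the closing sentence describes how outcomes are determined. This is fair, and it means one cannot say as settled fact that the endpoint will be decided from a different source in each arm. It does not resolve the matter: the arm-specific sentences say how compliance and adherence are assessed, and no source is given priority. Nor is this a detail left to a fuller document, because the conflicting statements are in the text.

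A second reply concerns direction. The large false-positive figures assume that every true completer in the intervention arms is captured. That objection stands: the last three rows of the table show the gap shrinking or changing sign.

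A reader might also infer three stronger claims that the text does not support.

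- That the game pays participants to declare doses. Strategy 2 awards coins for reading information and for giving information about partners. It ties passing a phase to having taken the doses, and does not say how this is verified.
- That contacting usual-care participants would contradict the Study design section. That section says of conventional care that "it does not consist of an active search through home visits or telephone contacts". One contact to ascertain an outcome is not an active search.
- That usual care rests on a single unit's record. Strategy 3 refers to public health records, and the closing sentence to the unit where treatment took place.

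**Conclusion.** The point holds for treatment adherence, the primary outcome. The protocol assigns arm-specific sources, adds an unassigned general statement, and leaves the deciding source open; these passages must be reconciled. Followed as written, the plan allows misclassification to depend on the arm in every between-arm contrast. For VDRL completion the split is explicit for telephone and usual care and only inferred for the app arm.

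The direction is likely to favour the interventions, but is not certain. In the scenarios at 16.5% true completion and 51 per arm, the spurious difference lies between about −3 and +20 points, and the chance of falsely favouring an intervention between about 1% and 69%, against a nominal 2.5%. The upper end is an extreme scenario. All error rates are assumptions; what rests on the text is that the sources differ and that none is named as decisive.

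**What to change.** Replace the arm-specific sentences in Outcome assessment, and align Strategy 3, with one rule for all arms.

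- Decide the primary outcome, and VDRL at 3, 6 and 12 months, from dated entries in the health-unit or public health record at the unit or units where the participant was treated.
- Abstract the records in the same way and at the same time points in every arm, where feasible without knowledge of the arm.
- Collect self-declaration identically in all arms and report it as a sensitivity analysis.
- Use game uploads, app use and call data only as process measures.

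A stated hierarchy of both sources, applied identically in all arms, would also remove the ambiguity.

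The cost is a wording change plus record retrieval for the two intervention arms; contact with the units is already planned. The sample size stays at 51 per group. Some doses given but not recorded will be missed. The method of missing them would be common to all arms, but equal losses cannot be guaranteed, because an intervention might change where people are treated.
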